##### Early supervised ambulation—‘walk’

The standardised ambulation protocol [16, 17] (Table 2) will be provided as soon as practical after surgery by a physiotherapist. Patients will receive one supervised ambulation session per day until a threshold score is met [18] (Additional file 1), or discharge from hospital, whichever occurs first. At every session, the participant will be progressed sequentially through the protocol stages aiming to achieve a walking time of at least 10 min, but no more than 15 min, at an intensity of at least three on the Borg 10-point visual analogue scale (VAS) of perceived exertion [19], and where breathing is deeper than at rest. The treating physiotherapist will use a stopwatch to ensure the treatment session does not exceed 15 min and can provide a walking aid if clinically indicated. If necessary, ambulation sessions can comprise of equal work/rest intervals. Shorter, but not longer, rest times are allowable. The final achieved ambulation stage corresponds to total time walked, including the marching on the spot time, and not including rest periods.

**Table 2 Tab2:** ICEAGE ambulation protocol

Stage 1 (safety)	Sit over edge of bed/sit in chair minimum of 2 min
Stage 2 (safety)	March on spot 0–1 min
Stage 3 (ambulation)	March on spot/walk away from bedside 1–3 min
Stage 4 (ambulation)	March on spot/walk away from bedside 3–6 min
Stage 5 (ambulation)	Walk away from bedside 6–10 min
Stage 6 (ambulation)	Walk away from bedside 10–15 min
Stage 7 (ambulation)	Walk away from bedside > 15 min
Provide assisted early ambulation as soon as possible on the first postoperative day. At each session, progress through each stage in sequence. Time achieved in the session is accumulative. Aim to achieve rating of perceived exertion of greater than 3/10. Aim to assist patient to ambulate more than 10 min (stage 6 or greater). Once patient is able to ambulate past stage 3, patient can be assisted to ambulate with a physiotherapy assistant, as long as safe to do as determined by the ward physiotherapist. Interval training is permissible to obtain target walking time. Each interval of rest time must not exceed the preceding work time. Total session time is the accumulative work time. Provide assisted early ambulation once a day until discharged according to the discharge scoring tool.	

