##### Supervised early rehabilitation—‘exercise more’

Intervention participants will receive physiotherapist supervised early rehabilitation lasting at least 30 min provided at least once daily. Rehabilitation will consist of a combination of ambulation and non-ambulatory chair- or bed-based exercises (Fig. 2) starting as soon as possible after surgery and continuing daily thereafter for at least the next five postoperative days or until at least five daily sessions are delivered. Exercises will be provided in a top-down hierarchical sequence starting from ambulation and aiming for the maximum physical activity type the participant is able to attempt. Exercise delivery progresses sequentially down the protocol until at least 30 min of activity have been accumulated. For example, participants will first be assisted to ambulate for at least 15 min with a goal to achieve at least 30 min. If time ambulated is less than 30 min, the participant will attempt resistive lower limb exercises in standing for the remaining time or until fatigue limits the performance. If time still remains less than 30 min, participants will attempt upper limb/lower limb resistance exercises in sitting until fatigued. This process continues until a minimum total treatment time of 30 min has been reached. A treating physiotherapist is also permitted to prescribe a personalised training activity based on a detected functional deficit to be incorporated within the rehabilitation programme. These targeted and individualised sessions will be recorded.

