All sessions will be conducted by a physiotherapist until at least the fifth postoperative day unless the supervising physiotherapist is confident that a therapy assistant or the participant will undertake the rehabilitation programme exactly as prescribed for the minimum 30 min. After the fifth postoperative day, daily treatment with a physiotherapist or therapy assistant will continue until either a referral for sub-acute rehabilitation services is made (see endpoints), a participant is discharged from hospital, or once a threshold score is met [18] (Additional file 1), whichever occurs first. If the patient meets the discharge score prior to the fifth postoperative day, daily treatment will continue until the fifth postoperative day but cease thereafter.

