#### Secondary/exploratory trial outcomes

In hierarchical order:Referral by the surgical team or other allied health professional within the first 14 postoperative days for additional acute-ward physiotherapy rehabilitation, sub-acute hospital rehabilitation, or community-based rehabilitation. On receipt of a referral, or by the 14th postoperative day if referral not received, a blinded senior physiotherapist will review the participant’s current medical record and adjudicate for the requirement for rehabilitation services.Discharge destination from the acute hospital ward (home, rehabilitation facility, nursing home, or other hospital);Hospital LOS in days. This is defined as continuous days spent in any type of inpatient hospital service (i.e. acute care, sub-acute rehabilitation, or time at another hospital) from the day of admission for acute condition to the day of discharge to community. Hospital days will be sub-categorised into acute and sub-acute;Incidence of a prolonged postoperative ileus (PPOI) anytime from the fourth to the 14th postoperative hospital day. A PPOI is defined if two or more of the following criteria are met on or after the fourth postoperative day [30]: (i) nausea or vomiting, (ii) inability to tolerate an oral diet over last 24 h, (iii) absence of flatus over the last 24 h, (iv) abdominal distension, and (v) radiologic confirmation. The day which PPOI is first diagnosed is the day of PPOI onset for purposes of time-to-event analysis.Diagnosis of pneumonia defined as the presence of new CXR infiltrates along with at least two of the following: temperature > 38 °C, dyspnoea, cough, and purulent sputum, altered respiratory auscultation, and white cell count > 14,000/ml or leukopenia < 3000/ml on any day within the first 14 postoperative hospital days;Recovery of physical function and QOLi)Rate of change of the Modified Iowa Level of Assistance [31] (mILOA; Additional file 1) score over four measures taken second daily from the first postoperative day and a final score on the day of acute-ward discharge. The mILOA consists of four mobility tasks (supine to sitting on the edge of the bed, sit to stand, walking, and negotiation of one step), which are graded according to the level of assistance required, use of gait aid, and the distance that can be walked. Data will be extracted from the medical and physiotherapy records to score;ii)Rate of change in handgrip strength (kg) measured using a handheld dynamometer over four postoperative measures within the first 14 days. Measures will be taken at least 2 days apart;iii)Rate in change of the EuroQual QOL score [32] (EQ-5D; Additional file 2); measures to be taken directly from the patient over two consecutive measures separated by 48 h, within the first five postoperative days, and at 90 days following surgery;iv)Health-related QOL using World Health Organisation Disability Assessment Schedule V2 [33] (WHODAS; Additional file 3) change from self-rated status in the week prior to surgery, to day of discharge from acute care, and at 90 days following surgery;v)Physical capacity using Self-Assessment of Physical Activity Questionnaire [34] (SAQ; Additional file 4) from self-rated capacity regarding the week prior to surgery to 90 days following surgery;vi)Time in hours from end of operation to time able to achieve ambulation greater than 1 min;vii)Time in days from end of operation to achieve ambulation greater than 10 min;ICU LOS in days;Unplanned ICU admission during acute hospital stay;Mortality—in-hospital, 30 and 90days, and at 1 year;Sepsis within the first 7 days according to the Sequential Organ Failure Assessment (SOFA) for ICU patients and quick-SOFA for ward patients [35];Time in days to discharge from physiotherapy as determined daily using the Post-Operative Physiotherapy Discharge Scoring Tool [18] (Additional file 1);Time in days to readiness for hospital discharge within the first 14 postoperative days defined by standardised scoring criteria [36];Patient reported complications at 90 days using a standardised semi-structured interview [16];Hospital costs for the admission episode of care supplied by the participating centres’, or health departments’, costing data for each participant’s admission episode.

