### Blinding

The recruiting and treating physiotherapists will be solely aware of group allocation. Assessments of primary and secondary outcomes and data collection will be performed by independent masked assessors not involved in the participant’s care. Assessors will require access to the medical record. To ensure masking to group allocation, documentation of physiotherapy assessments and interventions will be written to a standardised format (Additional file 5) with treatment recorded ‘Treatment provided as per ICEAGE protocol’. Documentation detailing physiotherapy treatment will be recorded separately and stored securely by the treating physiotherapist until the 14th postoperative day, the day of discharge, or until a defined endpoint is met, whichever occurs first, at which point the physiotherapy treatment documentation will be integrated into the medical record.

All doctors, surgeons, nurses, discharge coordinators, data analysts, and statisticians will be blinded to group allocation. If a participant inadvertently informs an assessor of their specific physiotherapy treatment, this will be reported, and a new assessor will be found for ongoing assessments.

It is anticipated that participants will be blinded to group allocations as both arms receive physiotherapy. A convenience sample of 30 consecutive participants will be asked which group they believed they had been allocated at the 90-day follow-up interview.

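### Masked assessment is claimed for all secondary outcomes, but the ambulation times and part of mILOA rest on observations by unmasked treating staff, and for item vii and session-based mILOA the chance to be observed differs by arm.

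*Protocol article*

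**What the plan says.** **Masking.** The Blinding section states that only the recruiting and treating physiotherapists know the allocation, and that primary and secondary outcomes are assessed by "independent masked assessors not involved in the" participant's care. Physiotherapy notes follow a standard format that hides the treatment, and the treatment detail is stored separately. The Discussion relies on masking of all assessors when it attributes effects to the additional therapy.

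**Outcomes.** Three of the seven physical-recovery items in Secondary/exploratory trial outcomes matter here.
- Item i, mILOA, is scored "over four measures taken second daily from the first postoperative day and a final score on the day of acute-ward discharge". Its source is given as "Data will be extracted from the medical and physiotherapy records to score".
- Item vi is "Time in hours from end of operation to time able to achieve ambulation greater than 1 min".
- Item vii is "Time in days from end of operation to achieve ambulation greater than 10 min".

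**Sessions.** In control, "Patients will receive one supervised ambulation session per day until a threshold score is met", or until hospital discharge. In intervention, "If the patient meets the discharge score prior to the fifth postoperative day, daily treatment will continue until the fifth postoperative day". In intervention sessions "participants will first be assisted to ambulate for at least 15 min with a goal to achieve at least 30 min"; control sessions are capped at 15 min.

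**The concern.** The masking statement covers every secondary outcome, but these three items draw on what happens in treatment sessions. The person running the session knows the arm, decides how much help to give and writes the record. If the two arms also differ in how long and how often patients are tried, a difference in item vii or in mILOA may partly show who was given the chance to be recorded rather than who recovered faster. A reader who takes the Blinding section and the Discussion at face value would treat such a difference as masked evidence of recovery.

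**Working it through.** The plan gives no figure for this point, so the check sets its sections side by side.

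**1. Where the observations come from**
- Early supervised ambulation: the time from surgery to the first successful ambulation is recorded as part of the supervised protocol.
- Other components of postoperative care: walking done alone or with other ward staff is not measured.
- Items vi and vii can therefore come only from treatment sessions. These are run by the treating physiotherapist, or by an assistant working to that arm's prescription.
- mILOA uses both the medical and the physiotherapy record, so at least part of it has the same source.

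The Blinding section can hold for the person who extracts the data. It does not hold for the observation that is extracted.

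**2. Whether the opportunity to be observed is equal**

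| Feature | Control | Intervention | Bears on |
|---|---|---|---|
| Threshold score met before day 5 | Sessions stop | Sessions continue to day 5 (also in Protocol endpoints) | vii, session-based mILOA |
| Sessions per day | One | At least one | vii |
| Same-day repeat | If unavailable or not past 1 min | Also permitted to reach 30 min | vii |
| Starting activity | Ambulation protocol | Same protocol first (Table 1, item 4) | vi: no difference |
| Stop on rehabilitation referral | Yes | Yes | no difference |

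Consider a patient who walks 5 min in the day's session. In control there is no provision for a second attempt that day. In intervention a further session may be tried, and it could pass 10 min. Likewise, a control patient who met the threshold score without yet walking more than 10 min would have no later session in which to record the event. The plan analyses these times by Cox regression, and a stop that depends on recovery is not independent of the event being timed.

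**3. mILOA points at stake, under an assumption**

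Second-daily scoring from day 1 gives days 1, 3, 5 and 7, plus ward discharge. Suppose the threshold is met on day 2 and only session notes can supply a score.
- Control: sessions end on day 2, so 1 scheduled day is covered (day 1).
- Intervention: sessions end on day 5, so 3 scheduled days are covered (days 1, 3 and 5).

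Both patients also have the ward-discharge score. The gap shrinks with every mobility entry in the medical record.

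**4. Scale for item vii, on an assumed input**

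Let f be the proportion by which unequal opportunity lowers the control hazard of a recorded pass, with true recovery equal. The apparent hazard ratio is then 1/(1 − f).
- f = 5%: 1/0.95 = 1.05
- f = 10%: 1/0.90 = 1.11
- f = 20%: 1/0.80 = 1.25
- f = 30%: 1/0.70 = 1.43

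Nothing in the article fixes f, so this is a scale and not an estimate.

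**The case against.** The case on the other side is substantial, and it limits the point.

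- **The control target.** A reader might infer that item vii is biased because the control goal sits at the 10-min threshold while the intervention goal is 15 to 30 min. The document does not support this. Table 2 aims for more than 10 min (stage 6 or greater), the 15-min cap lies above the event, and intervention sessions begin with the same ambulation protocol. The higher intervention targets lie beyond the event.
- **Loss of observation.** A reader might also infer that control patients are no longer seen after the threshold score. The text stops treatment, not outcome assessment. The mILOA schedule is the same in both arms and includes a discharge score, and the medical record is a second source. The 1-versus-3 count is therefore conditional.
- **Item vi.** The threshold, the start and the initial protocol are the same in both arms. Only the unmasked observer remains as a weakness.
- **Masking.** A masked assessor working from standardised notes fits the Blinding section. This stands for the extraction, but it does not reach the source observation.
- **Importance.** The recovery claim does not rest mainly on these items. Rehabilitation referral, discharge destination and length of stay rank above them, and handgrip, EQ-5D, WHODAS and SAQ stand beside them.

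The threshold tool is in Additional file 1, which is not shown. How often a control patient stops before passing 10 min is therefore unknown.

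**Conclusion.** The point holds in a limited form. The masking statement is too broad for items vi and vii, and for mILOA as far as it uses physiotherapy notes. Unequal opportunity to be observed is a further weakness of item vii and of session-based mILOA, but not of item vi. It arises from the stopping rule and the repeat-session rule, not from the walking targets.

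The size of the effect cannot be determined. It depends on how often control patients meet the threshold before walking more than 10 min, how often intervention sessions are repeated, and how much mobility information the medical record holds. These are secondary/exploratory outcomes, and the primary outcome and its sample size are untouched. What changes is how much weight a difference in these items can bear.

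**What to change.** 1. Qualify the Blinding section and the Discussion: mILOA and the ambulation times rest on observations by unmasked treating staff, even where a masked person extracts them.
2. Report item vii as a treatment-delivery measure, or as an outcome partly determined by allocation, and not as masked evidence of recovery. Keep item vi as an outcome with the unmasked caveat.
3. For remaining patients, where feasible, have the blinded assessor who already attends daily to day 7 for the primary outcome score mILOA on the same scheduled days in both arms, whether or not physiotherapy has ended. Do not carry scores forward: that would freeze discharged patients at an earlier value and defeat fixed-day scoring. Record which method produced each score.

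Items 1 and 2 need only wording. Item 3 adds a task to existing visits. Because recruitment began in June 2015 and was expected to finish in late 2018, it would leave mILOA collected by two methods. A few exploratory outcomes would carry less weight. No treatment rule changes.

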**Fig. 3 Fig3:**
[figure not shown]
ICEAGE schedule of events and timeline. Abbreviations: POD postoperative day, D/C hospital discharge, SAQ specific activity questionnaire, WHODAS World Health Organisation disability assessment score, EQ-5D EuroQuol five domains, PPC postoperative pulmonary complication, PPOI prolonged postoperative ileus, ICU intensive care unit, LOS length of stay, mILOA modified Iowa level of assistance

### Protocol endpoints

Treatment protocols will be ceased when:Participant is discharged or transferred from the primary treating hospital.Participant becomes deceased or death is expected within next 7 days.Participants meet a threshold score to trigger discharge from physiotherapy treatment^18^. This criterion is delayed for the first five postoperative days for intervention participants.A confirmed PPC diagnosis ceases the respiratory treatment protocol. Respiratory treatment is then provided at the discretion of the ward physiotherapist. Participants remain being treated with the rehabilitation protocol as per group allocation.A confirmed referral for additional sub-acute rehabilitation services ceases the ambulation or early rehabilitation protocol. Rehabilitation is then provided at the discretion of the ward physiotherapist. Participants remain being treated with the respiratory treatment protocol as per group allocation.

### Blinding

The recruiting and treating physiotherapists will be solely aware of group allocation. Assessments of primary and secondary outcomes and data collection will be performed by independent masked assessors not involved in the participant’s care. Assessors will require access to the medical record. To ensure masking to group allocation, documentation of physiotherapy assessments and interventions will be written to a standardised format (Additional file 5) with treatment recorded ‘Treatment provided as per ICEAGE protocol’. Documentation detailing physiotherapy treatment will be recorded separately and stored securely by the treating physiotherapist until the 14th postoperative day, the day of discharge, or until a defined endpoint is met, whichever occurs first, at which point the physiotherapy treatment documentation will be integrated into the medical record.

All doctors, surgeons, nurses, discharge coordinators, data analysts, and statisticians will be blinded to group allocation. If a participant inadvertently informs an assessor of their specific physiotherapy treatment, this will be reported, and a new assessor will be found for ongoing assessments.

It is anticipated that participants will be blinded to group allocations as both arms receive physiotherapy. A convenience sample of 30 consecutive participants will be asked which group they believed they had been allocated at the 90-day follow-up interview.

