**For ventilated patients, if FiO_2_ ≥ 0.5 or PEEP ≥ 8, assume criterion 3 is present (do not alter FiO_2_), for all other patients set FiO_2_ to 0.21 and observe SpO_2_ for 2 min. If SpO_2_ drops below 90%, immediately reinstate previous FiO_2_. If not permissible to alter ventilation parameters, assume positive

^#^If no written report for a CXR is available and a patient has three other positive signs, a masked senior physiotherapist or ward medical officer is to be contacted to report verbally on the available CXR

***When there are no daily measures of CXR or sputum sampling, carry over a positive finding to the next consecutive postoperative day

Participants are assessed prospectively and daily for a PPC by a blinded assessor until the seventh postoperative day. From the 8th to the 14th postoperative day, additional PPC assessments are performed only as clinically suspected based on signs or symptoms of respiratory system deterioration reported within the medical record. To reduce the potential for missing data, retrospective collection of PPC data from the medical record will be permitted when a patient or assessor is unavailable for PPC assessment. Diagnostic components (chest X-ray (CXR), white cell count, sputum microbiology) are recorded only if results are available. All medical officers are masked to group allocation, and these diagnostic tests are ordered only as clinically indicated, and not routinely for the purposes of the ICEAGE trial.

For this trial, modifications have been made to reduce delays to possible diagnosis of a PPC (Table 3). An automatic positive threshold for the hypoxemia criterion has been set for ventilated patients; a positive CXR and/or sputum sample finding can be carried over to the next postoperative day if serial testing was not performed; a CXR can be verbally reported by a blinded senior respiratory physiotherapist or physician, rather than awaiting a radiologist report; and when three factors (out of a possible eight) are present, the blinded site investigator or ward physiotherapist will discuss the option of further diagnostic testing to confirm PPC with the participant’s treating physician. Additionally, patients with three out of eight criteria will be assessed twice daily for any clinical deterioration.

Any suspected PPC will be confirmed by a blinded senior physiotherapist, and the participant will then receive respiratory treatment as determined by the ward physiotherapist.

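### Filing physiotherapy treatment notes in the medical record once an endpoint is met can unmask assessors who are still scoring PPC or adjudicating rehabilitation need

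*Protocol article*

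**What the plan says.** **Release rule.** Under Blinding, the detail of physiotherapy treatment is recorded apart from the medical record so that assessors stay masked. It is held back "until the 14th postoperative day, the day of discharge, or until a defined endpoint is met, whichever occurs first". Once one of these occurs, the notes are filed in that record. The same section states: "Assessors will require access to the medical record". Its only remedy for unmasking, a replacement assessor, applies when a participant lets slip what treatment they received.

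**Endpoints.** Protocol endpoints lists events that stop all or part of the treatment protocol: discharge or transfer, death or expected death, a confirmed PPC, a confirmed referral for sub-acute rehabilitation, and the discharge score ("Participants meet a threshold score to trigger discharge from physiotherapy treatment"). On the last of these it adds: "This criterion is delayed for the first five postoperative days for intervention participants".

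**Assessment still running.** Under Primary outcome, the outcome is the first PPC within 14 postoperative hospital days. It is assessed daily to day 7 and then to day 14 when entries in the record raise suspicion. In addition, "retrospective collection of PPC data from the medical record will be permitted" when the patient or assessor is unavailable. Under Secondary/exploratory trial outcomes, the first-ranked outcome is rehabilitation referral. On receipt of a referral, or by day 14 without one, a blinded senior physiotherapist is to review the "current medical record and adjudicate for the requirement for rehabilitation services".

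**The concern.** The separate notes exist to protect masking, yet the rule can end that protection before the masked work is finished. A participant may reach an endpoint on the ward with days of PPC scoring or the rehabilitation adjudication still to come. From then on, the record the assessor must open contains the treatment detail. Nothing in the plan covers disclosure by the record, and a replacement assessor would read the same record.

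Some PPC criteria involve judgement (breath sounds, sputum, a verbal chest-film report where no written one exists), as does the need for rehabilitation. The Discussion relies on masked assessors to attribute any effect to the additional therapy. The exposure is also partly uneven between arms, because the discharge-score endpoint becomes available earlier to controls. Doctors and nurses, who are declared blinded, use the same record; a physician's diagnosis is itself a PPC criterion.

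**Working it through.** The point is procedural, so the main check sets the sections side by side.

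**1. Which triggers can fall while masked assessment is open?** Blinding does not cross-reference its term for an endpoint. Protocol endpoints is the only section that defines any, so I read the two together.

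| Trigger | Primary outcome (first PPC, in hospital, to day 14) | Rehabilitation adjudication (at referral or by day 14) |
|---|---|---|
| Discharge score met in hospital | Exposed: PPC scoring continues | Exposed if adjudication comes later |
| Confirmed PPC | Not exposed: the event is already counted | Exposed if adjudication comes later |
| Confirmed referral | Exposed: PPC scoring continues | Exposed only if confirmation precedes adjudication |
| Discharge | In-hospital window closed; exposed only through later retrospective collection | Exposed if adjudication comes later |
| Day 14 | Window ends; exposed only through later retrospective collection | Release and adjudication limit fall on the same day, with no stated order |

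Death closes the in-hospital window. Expected death is also a listed endpoint and could precede death, but I do not rely on it.

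**2. Does the timing itself reveal the arm?** For intervention participants the discharge-score criterion does not operate until day 5. The section on supervised early rehabilitation agrees: a score met before day 5 does not stop treatment until day 5. Notes filed on this trigger before day 5 can therefore come only from a control participant. Daily PPC scoring runs to day 7, so such a release falls inside the daily scoring period.

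**3. The plan's own figures.** Inputs from Sample size: 20% v 8%, alpha 0.05 (two-sided assumed), power 80%.

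n per arm = [1.96·√(2 × 0.14 × 0.86) + 0.8416·√(0.20 × 0.80 + 0.08 × 0.92)]² / 0.12² = (0.962 + 0.407)² / 0.0144 ≈ 130.1, so 131 per arm and 262 in total, as stated. Also 262 × 1.10 = 288.2, which matches the target of 288. The planned events are 0.20 × 131 = 26.2 and 0.08 × 131 = 10.5, a difference of 15.7. This is the effect the trial is powered for and says nothing about the size of any bias.

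**4. Illustration under assumptions.** The documents do not say how many participants reach an endpoint early. Assume no true effect, 20% in both arms and 131 per arm. Let a share f of one arm's PPCs be assessed after release, with a relative under-detection d among them. Both f and d are assumed.

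- Observed rate in that arm: p₂ = 0.20 × (1 − f·d), with D = 0.20 − p₂
- SE₀ = √(2·p̄(1 − p̄)/131), with p̄ the mean of 0.20 and p₂
- SE₁ = √((0.20 × 0.80 + p₂(1 − p₂))/131)
- Two-sided rejection rate = Φ((D − 1.96·SE₀)/SE₁) + Φ((−D − 1.96·SE₀)/SE₁)

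| f | d | p₂ | p₂/0.20 | Rejection rate |
|---|---|---|---|---|
| 0.10 | 0.10 | 0.198 | 0.99 | 5.0% |
| 0.25 | 0.25 | 0.1875 | 0.94 | 5.75% |
| 0.25 | 0.50 | 0.175 | 0.875 | 8.1% |
| 0.50 | 0.50 | 0.150 | 0.75 | 18.6% |

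The range runs from negligible to material. Which arm would be affected, and in which direction, is equally unknown.

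**The case against.** A reader might infer that blinding fails for the whole trial. The text does not support that, and most of the opposing case stands as a limit on scope:

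- **Primary outcome.** A confirmed PPC releases notes only after the event is counted, and discharge closes the window apart from retrospective collection. After day 7, PPC assessment takes place only on suspicion.
- **Every adjudication exposed.** Not shown. The referral endpoint must be confirmed, and confirmation may be the adjudication itself, in which case release follows it. Review by day 14 may also precede release on that day.
- **Partial endpoints.** A PPC or a referral stops only one treatment component. Blinding does not say whether such a partial stop releases all the notes; the wording allows it.
- **mILOA.** The protocol says "Data will be extracted from the medical and physiotherapy records to score", which may suggest unmasked scoring. But physiotherapy assessments are to be written in the standardised masked format, so a need for the withheld notes is not established.
- **Objective criteria.** A PPC needs four of eight criteria, several of them measured, and verbal film reading is restricted.
- **Other cues.** Treatment entries in the ordinary record could stop earlier in controls whatever happens to the detailed notes.

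What the objection does not remove is the discharge-score and referral route to the primary outcome, the prior discharge-score or PPC route to the adjudicator, and the absence of a safeguard against disclosure by the record.

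**Conclusion.** The concern holds in limited form. The release rule can defeat its own masking purpose for participants who reach an endpoint in hospital while assessment is open. For the primary outcome this means the discharge score, a confirmed referral, or retrospective collection after release. For the rehabilitation adjudication it means chiefly an earlier discharge score or confirmed PPC, with the shared day-14 limit a further weak point. Before day 5, the discharge-score release is specific to controls.

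The size is unknown. No frequency of early endpoints is given, and the scenarios above rest on assumed values. The planned gap of about 16 events must not be read as an estimate of bias. The conclusion assumes that the endpoints meant under Blinding are those listed under Protocol endpoints. Because unmasking cannot be undone after the event, prevention is the proportionate response.

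**What to change.** For participants still to be enrolled, change the release rule in one of two ways:

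1. Integrate the treatment notes only once two things are completed and locked: the last masked in-hospital assessment (PPC, PPOI and pneumonia to day 14 or discharge, including any retrospective collection) and the rehabilitation adjudication.
2. Alternatively, give assessors and the adjudicator a record extract without the treatment notes. This protects them but not the ward clinicians who read the full record.

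In either case, state which endpoints the release rule refers to and whether a referral is confirmed before or after adjudication. Log each release date against the assessment dates, so that exposure among participants already assessed can be reported.

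**Cost.** This is a record-handling amendment; treatment, outcome definitions and sample size are unchanged. Some notes are held separately for longer, though sites already hold them for up to 14 days. Recruitment began in June 2015 and was expected to finish in late 2018, so the change reaches only the remaining participants. It does not remove any cue from routine treatment entries stopping earlier in the control arm.
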